#### c) Other outcomes

i) *Fetal birth outcomes *and ii) *Maternal birth outcomes *will also be compared on an intention to treat basis between the 2 groups in the first analysis at delivery (as *a *&*b *above)

As these outcomes relate to the safety of NRT in pregnancy we will also conduct an analysis of these outcomes comparing participants in each group who report using any patches with those in each group who report using none.

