## Background

Maternal smoking during pregnancy harms unborn children and, as up to 30% of pregnant women smoke [1], it is a significant public health problem. The adverse effects of smoking during pregnancy include an increased risk of miscarriage and stillbirth, accounting for 4000 deaths annually, and of pre-term birth and low birth weight leading to increased perinatal morbidity [2,3]. Children of mothers who smoke whilst pregnant are at increased risk of neo-natal mortality, sudden infant death syndrome and asthma [2]. Maternal smoking whilst pregnant is also associated with an increased risk of attention deficit and learning problems in childhood [3,4]. Currently only around 25% of pregnant smokers stop for even part of their pregnancy and, of these, around two thirds re-start post-natally [1].

Effective methods for promoting smoking cessation by pregnant women are required. The most effective smoking cessation therapy in non-pregnant smokers is a combination of behavioural support and pharmacotherapy with either nicotine replacement therapy (NRT) [5] or bupropion [6]. Behavioural support alone can increase smoking cessation rates by up to 7% [7] and the addition of pharmacotherapy increases this further by 1.5 to 2-fold. Behavioural support is usually provided without pharmacotherapy, however, because of concerns that drug therapy may harm the fetus [8]. This is understandable for bupropion, but is far less logical for nicotine.

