### Treatment group

Pregnant women will receive an eight week course of 15 mg/16 hr NRT transdermal patches. Although many studies have used longer courses, there is no evidence that these are more effective [5]. Patches will be issued in conjunction with individual behavioural support (*Section 10*) which is an effective smoking cessation intervention in pregnancy [7]. Four weeks after their quit dates, women who are not smoking will be issued with a second four week supply of patches.

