### Withdrawal from patch treatment

If for any reason, a participant terminates patch treatment, every effort must still be made to collect follow up data.

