#### c) Upon admission for childbirth

The following data are recorded by the RM or delivery suite staff:

Date of follow up/exhaled CO reading or saliva sample

Smoked at all in the 24 hrs prior to delivery

Smoked between quit date and delivery

One or both of, *i) exhaled CO reading & ascertainment date ii) saliva sample *(for cotinine)

On how many days have patches been used?

On how many days (if any) have non-trial patches been used?

How many behavioural support sessions with NHS stop smoking services used (telephone & face to face)?

i) These data obtained by RM from ***maternal ***or ***infant medical records before ***discharge. For reasons of data protection some personal infant details are recorded on paper rather than being transmitted over the internet to the trial database:

*maternal *

hypertension (>140/90) on 2 occasions (excluding labour)

miscarriage (between randomisation and 24 weeks)

labour onset (spontaneous, induced, no labour)

mode of delivery (SVD, instrumental, caesarean)

ante natal or post natal maternal hospital admission

*infant*

baby initials

D.O.B

Gender

Baby NHS number

*Prompt for RM to confirm full name and address and contact details of baby and to record these on paper *(see below)

Prompt for RM to make a new record of contact details if these have differed from previous (i.e. maternal) ones

baby hospital number

birth weight

Number of births

if multiple birth, indicate number and birth order

live or stillbirth?

cord ph < 7.0

Apgar <7 at 5 min

*Gestational age at birth *– to be calculated within database from gestation at recruitment

These infant personal details will be recorded on paper only:

baby name

baby address (inc postcode)

ii) These data obtained by research midwife from ***infant medical records after ***discharge:

If live birth? live on leaving hospital

ventilation > 24 hrs

necrotising enterocolitis

neonatal convulsions

admitted to special care

*intraventricular haemorrhage *(4 categories)

*congenital abnormality present (y/n). If y then free text to describe this*.

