### Interventions

Details of NRT patches are given earlier in this document and details of behavioural support follow. The first behavioural support session will be provided at recruitment by a research midwife who has been trained in smoking cessation methods in accordance with national standards [30] and who has dedicated time for this task. Models of behavioural support that are effective in pregnancy vary greatly[7] and in non-pregnant subjects, behavioural support following very different psychological models are all equally effective [31]. We will, therefore, standardise the first support session to include information on:

i) the harmful effects of smoking in pregnancy

ii) the role of nicotine addiction in sustaining smoking

iii) how to use NRT (including safety concerns)

iv) coping with withdrawal symptoms.

Support will be specific to the needs of pregnant women and may involve:

i) enlisting partner support

ii) a partner quit attempt

iii) ensuring that the partner has information about smoking cessation services

Study midwives will use brief cognitive – behavioural counselling, combining components from effective counselling strategies that are effective [31], such as:

i) providing structure to quit attempts

ii) agreeing a "contract" for any attempt

Counselling will be delivered in a manner that is consistent with routine clinical practice, using a format similar to that which has been effectively applied within routine ante natal care in the US [32]. A quit date which is within 2 weeks will be agreed and participants will be instructed to start using patches on this date.

Local NHS stop smoking services will provide up to 5 *subsequent behavioural support sessions*. These follow up sessions will reinforce women's reasons for quitting and strategies for success. A standardised approach to follow up support sessions is important and NHS stop smoking service staff will be orientated towards this.

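### The added safety contrast of patch users with non-users within each arm is confounded by quitting and should not be read as evidence on NRT safety

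*Protocol article*

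**What the plan says.** The protocol article, under c) Other outcomes, plans two analyses of fetal and maternal birth outcomes. In the first, they "will also be compared on an intention to treat basis between the 2 groups in the first analysis at delivery". The second is introduced by its purpose, "As these outcomes relate to the safety of NRT in pregnancy we will also conduct an analysis of these outcomes", and is defined as "comparing participants in each group who report using any patches with those in each group who report using none".

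Four other places bear on how to read the second analysis:

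- Interventions: a quit date is agreed, and "participants will be instructed to start using patches on this date".
- Treatment group: four weeks after the quit date, "women who are not smoking will be issued with a second four week supply of patches".
- Background: "The adverse effects of smoking during pregnancy include an increased risk of miscarriage and stillbirth". The same sentence goes on to pre-term birth and low birth weight.
- Data collection, at one month and on admission for childbirth: women are asked "On how many days have patches been used", and separately about non-trial patches.

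No adjustment, no role for the placebo-arm contrast and no caution on interpretation is stated for the user contrast. The cross-reference to parts a and b, where baseline adjustment and clustering are mentioned, is attached to the intention-to-treat sentence. Baseline adjustment would in any case not deal with quitting, which happens after baseline.

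**The concern.** Whether a woman uses a patch is her own decision, taken after randomisation. Because patches start on the quit date, women who use none are likely to include many who never made the attempt. If users stop smoking more often than non-users, their pregnancies differ in smoking exposure, which the protocol itself names as a cause of the outcomes being compared. The contrast then mixes any effect of the patch with the effect of quitting and with whatever else separates women who start from women who do not.

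Reverse causation is also possible. The quit date may fall up to two weeks after randomisation, so a pregnancy loss in that interval can place a woman among the non-users.

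The placebo patch contains no nicotine, so the placebo-arm contrast says nothing about nicotine. It shows only how users and non-users differ for other reasons. In the NRT arm, a benefit of quitting could be credited to the patch and could offset a direct harm within that contrast. The protocol offers the contrast as safety evidence, so a falsely reassuring result might be read as such.

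**Working it through.** **The plan's own figures.** The article gives no figure for this analysis. Its quit rates come from Sample size: 16% in controls and an odds ratio of 1.74. Odds 0.16/0.84 × 1.74 = 0.331, and 0.331/1.331 = 24.9%, which agrees with the stated 25%. Power with 500 per arm for 16% v 25% comes to 94.2%, against 93% stated. The quit rates are therefore usable as inputs; the power figure plays no part below.

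**Inputs**

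- From the protocol: overall quit rate q = 0.16 (placebo) and 0.25 (NRT); 525 women per arm.
- Assumed, not in the documents: effect of smoking on birth weight D = 150 to 250 g; share of non-users s = 0.10 to 0.20; quit rate in non-users n = 0.03 to 0.05; birth-weight SD 550 g.

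**Apparent difference with no direct nicotine effect**

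The quit rate in users must be (q − n·s)/(1 − s), so users minus non-users = (q − n)/(1 − s). The apparent birth-weight difference is D × (q − n)/(1 − s).

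| Arm | Low end (D = 150, s = 0.10, n = 0.05) | High end (D = 250, s = 0.20, n = 0.03) |
|---|---|---|
| Placebo | 150 × 0.11/0.90 = 18 g | 250 × 0.13/0.80 = 41 g |
| NRT | 150 × 0.20/0.90 = 33 g | 250 × 0.22/0.80 = 69 g |

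The NRT figures exceed the placebo figures because of the 9-point gap in quit rates: 150 × 0.09/0.90 = 15 g to 250 × 0.09/0.80 = 28 g. That part works through quitting brought about by NRT. The placebo figures reflect selection alone.

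**Effect on a real harm.** A direct harm of 50 g in NRT users (illustrative) would appear in the NRT-arm contrast as −50 + 33 = −17 g to −50 + 69 = +19 g.

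**Precision**

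- Within arm, users v non-users: SE = 550 × √(1/(525s) + 1/(525(1 − s))). At s = 0.20 this is 550 × √(1/105 + 1/420) = 60 g. At s = 0.10 it is 550 × √(1/52.5 + 1/472.5) = 80 g.
- Active v placebo among starters: SE = 550 × √(2/(525(1 − s))). At s = 0.20 this is 550 × √(2/420) = 38 g. At s = 0.10 it is 550 × √(2/472.5) = 36 g.
- Intention to treat: 550 × √(2/525) = 34 g.

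The within-arm contrast is thus both confounded and about twice as imprecise as either comparison between arms.

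**The case against.** **The randomised safety comparison is already in the plan.** This stands. A reader might infer that the trial cannot establish safety, or that nicotine harm would be hidden. The documents do not support that. Intention to treat comes first in the same section, and the Safety section gives the data monitoring committee birth outcome data to compare the study groups. The criticism reaches only the added contrast.

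**The contrast is made in each group, so the placebo arm acts as a negative control.** It could, but the article does not say so. Nor does subtracting one contrast from the other settle the matter. Because quit rates differ by arm, 15 to 28 g remains on the inputs above even if non-users quit equally often in both arms. The SE is √2 × 60 = 85 g to √2 × 80 = 113 g.

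**Users may not smoke less.** This stands in part. Every woman agrees a quit date before randomisation, one patch is enough to count as any use, and resupply conditional on not smoking bears more on the amount of use than on any v none. Heavier smokers might be more inclined to use patches. The direction of the bias is plausible, not established.

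**Larger biases are tempting to quote.** Taking 40% abstinence in users and 5% in non-users gives 250 × 0.35 = 88 g. With 10-20% non-users, overall abstinence would then be 0.40 × 0.80 + 0.05 × 0.20 = 33% to 0.40 × 0.90 + 0.05 × 0.10 = 36.5%. That conflicts with the protocol's 16% and 25%.

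**Women with unknown use.** A reader might infer that they are dropped, but the article does not say how they are handled. The instruction "If for any reason, a participant terminates patch treatment, every effort must still be made to collect follow up data" is sound and counts against heavy loss.

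**An analysis plan not shown may add cautions or other exposure analyses.** It may, so it cannot be said that this is the only such analysis. But the contrast itself is fixed here, with its safety purpose.

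**Conclusion.** The point holds for the supplementary contrast. As written, it is a non-randomised comparison, defined by behaviour after randomisation, tied to quitting and stated without adjustment or caution. Neither arm's result should be read as evidence on NRT safety.

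On the stated assumptions and the protocol's quit rates, users' babies could appear about 18-41 g (placebo) and 33-69 g (NRT) heavier with no direct nicotine effect. The smoking effect, uptake, non-user quit rate and SD are all assumed, so these figures show a plausible order of size. The actual size and direction are unknown.

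This is worth correcting because safety is a stated aim and a better comparison is available from data already being collected. It does not undermine the trial's main safety comparison.

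**What to change.** 1. State that intention to treat remains the basis for conclusions on safety.
2. Make the supplementary exposure analysis active v placebo among women who used at least one trial patch. Participants and research midwives are blind to allocation, so starting should not depend on arm and the two sets of starters should be comparable.
3. Optionally add a complier-average estimate with randomised arm as instrument. The exposure must be nicotine-patch use, not days of any patch, because both arms wear patches. Non-trial patches, already recorded, should count as nicotine exposure in either arm.
4. If the user v non-user contrast is kept, label it exploratory and non-causal, name the placebo arm as its negative control, and say whether non-trial patches count as any patches.

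The cost is analysis wording only; sample size and data collection do not change. There are two downsides. Women who never used a patch do not contribute to the supplementary comparison. And it estimates the total effect of NRT, including any effect through quitting: on the inputs above, 15-28 g of the starters' difference would come by that route. Neither it nor intention to treat isolates a direct effect of nicotine, and the report should say so.

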#### d) Sub group analyses

These will be conducted to investigate the relationship between i) baseline cotinine levels and cessation and ii) maternal educational level (proxy for socio-economic status) and cessation. We will model the relationship between smoking cessation, pre-treatment plasma cotinine levels and treatment group in a logistic regression, to establish whether there is effect modification by pre-treatment plasma cotinine and whether efficacy at given levels of plasma cotinine varies. The model will also establish whether or not smoking cessation is constant across all levels of pre-treatment plasma cotinine in the NRT group, or reduces with increasing pre-treatment plasma cotinine, which could be indicative of inadequate replacement of nicotine. We will use similar methods to investigate ii) above.

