It has recently become apparent that conventional doses of nicotine contained in NRT may be insufficient for pregnant women and this may explain the negative findings from the one trial of NRT in pregnancy. In pregnancy, the metabolic clearances of nicotine and cotinine (the principal metabolite of nicotine) are increased by 60% and 140% respectively. [15]. Accordingly, even when pregnant women take standard doses of NRT for adequate periods, these may still be ineffective because they may require higher doses of NRT to replace the nicotine they would have received via smoking. Higher doses of NRT might, therefore, be needed in pregnancy, but because there is very little human-subject research into the effects of nicotine on the developing fetus, it is not known whether these might increase the risk of fetal damage. Until the effectiveness of the current conventional dose of NRT is established, it is hard to justify trials of higher ones.

In summary, although consensus opinion suggests that taking NRT during pregnancy is likely to be safer than smoking [8,10,11,16], there is little direct trial evidence to support this and we do not know if NRT is actually *effective *in promoting smoking cessation amongst pregnant smokers. The *SNAP *trial will produce direct evidence on these important questions and will investigate whether or not NRT is more effective than placebo in achieving smoking cessation for women who and are between 12 and 24 weeks pregnant, who currently smoke 5 or more cigarettes daily and who smoked 10 or more cigarettes daily before pregnancy.

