### Sample size

We need to recruit 525 women into each arm of the study. A trial with 500 women in each arm would detect an absolute difference of 9% in smoking cessation rates between the two groups immediately before childbirth with a two-sided significance level of 5% and a power of 93%. We anticipate that up to 5% of women will be lost to follow up and inflate our sample size (of 500) by a factor of 1.05 to allow for this. This size of study would allow us to detect smaller treatment effects with lower power. For example, we would have 80% power to detect an absolute difference in cessation rates of 7%.

A Cochrane review has shown that approximately 10% of women who are still smoking at the time of their first antenatal visit will stop smoking with usual care and a further 6% to 7% will stop as a result of a formal smoking cessation program using intensive behavioural counselling [15]. This means that in our control group (*placebo plus intensive behavioural counselling*) we can expect a smoking cessation rate of around 16%. The most recent Cochrane review of NRT, reports a treatment effect (odds ratio) for transdermal patches of 1.74 95%CI (1.57–1.93) [5]. Consequently, if we were to find NRT as effective in pregnancy as it is generally, we could expect a smoking cessation rate of approximately 25% in our treatment group (*NRT plus intensive behavioural counselling*).

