### Follow-up at one month after agreed quit date

Participants will return to the research midwife (RM) for further supplies of patches. To allow some flexibility this follow up will occur between 3 and 6 weeks after randomisation. The RM will ascertain women's smoking status and those who report not smoking regularly (confirmed by exhaled CO measurement) will be issued with a new trial treatment pack number (obtained by the RM from the online database) and will receive a corresponding treatment pack (containing 4 weeks' patches). A saliva sample to measure cotinine levels on treatment will be taken. The Trial Office will send a postal questionnaire asking about smoking status to women who do not return at one month. One postal and telephone reminder will be used. When women report continued smoking cessation and do not attend for further NRT, the research midwife will contact them to arrange CO validation of this, visiting them at home, if necessary.

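### A falling quit rate with baseline cotinine inside the NRT arm cannot, on its own, separate inadequate nicotine replacement from cotinine predicting quitting in both arms

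*Protocol article*

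**What the plan says.** The protocol article, General statistical analysis plan, d) Sub group analyses, describes one model and two uses of it. The model: "We will model the relationship between smoking cessation, pre-treatment plasma cotinine levels and treatment group in a logistic regression". The first use compares the arms: "to establish whether there is effect modification by pre-treatment plasma cotinine and whether efficacy at given levels of plasma cotinine varies". The second looks inside the active arm: "The model will also establish whether or not smoking cessation is constant across all levels of pre-treatment plasma cotinine in the NRT group", or alternatively "reduces with increasing pre-treatment plasma cotinine, which could be indicative of inadequate replacement of nicotine". Nothing in that sentence makes the second reading depend on the slope in the placebo group or on the result of the effect-modification test.

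The Background explains why the question is asked. Nicotine and cotinine are cleared faster in pregnancy, so on standard NRT "they may require higher doses of NRT to replace the nicotine they would have received via smoking". The section gives this as a possible explanation for an earlier negative trial.

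**The concern.** The second use judges the NRT-arm slope against a flat line. The relevant comparator is the slope in the placebo arm. Baseline cotinine reflects how much a woman smokes and may well predict quitting with or without active patches. If it does, quitting falls with cotinine in the NRT group even though replacement is no worse for women with high cotinine. The placebo group measures this background relation, and the one-arm reading leaves it out.

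What is at stake is the interpretation of a secondary analysis. It is the analysis that the protocol links to whether the standard dose replaces enough nicotine. A misread slope could lend support to that explanation which the randomised comparison does not give.

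**Working it through.** **Inputs from the protocol (Sample size).** "We need to recruit 525 women into each arm of the study"; control quit rate about 16%; patch odds ratio 1.74; NRT quit rate about 25%; two-sided 5% level. The 25% follows from the other two: odds 0.16/0.84 × 1.74 = 0.331, and 0.331/1.331 = 24.9%. The stated power also reproduces closely: 500 per arm at 16% v 25% gives 94.2% (stated 93%), and 16% v 23% gives 79.9% (stated 80%). The protocol states no figure for the cotinine analysis itself.

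**Assumed, not in the documents.** Cotinine on a standardised normal scale, a value for every woman, and a common odds ratio per SD of 0.9, 0.8 or 0.7 in both arms. The value 1.0 (no prognostic effect) is shown for reference.

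**Model.** Let T = 1 for NRT and x = standardised cotinine:

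logit P(quit) = a + bT + cx + dTx

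The placebo slope is c, the NRT slope is c + d, and the interaction is d. A patch that works equally well at every level means d = 0. The NRT slope then equals c and is negative whenever c is negative. Testing c + d against zero therefore does not test d.

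**Approximate check.** The standard error of a slope near the null is about 1/√(n·p·(1−p)).

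- NRT arm at 25%: 1/√(525 × 0.25 × 0.75) = 0.101.
- Placebo arm at 16%: 1/√(525 × 0.16 × 0.84) = 0.119.
- Interaction: √(0.101² + 0.119²) = 0.156.

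The chance of a significantly falling NRT slope when d = 0 is Φ(|ln OR|/0.101 − 1.96):

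- OR 0.9: 0.105/0.101 = 1.05, giving about 18%.
- OR 0.8: 0.223/0.101 = 2.21, giving about 60%.
- OR 0.7: 0.357/0.101 = 3.54, giving about 94%.

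**Simulation.** 525 per arm, 3,000 trials per scenario (Monte Carlo standard error at most √(0.25/3000) = 0.9 points), Wald tests at two-sided 5%, no effect modification:

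| Common OR per SD | NRT slope significantly negative, quit rates 16%/25% | Same, 8%/10% | Interaction significant (both settings) |
|---|---|---|---|
| 1.0 | 2% | 3% | about 5% |
| 0.9 | 17% | 11% | about 4–5% |
| 0.8 | 59% | 33% | about 5% |
| 0.7 | 93% | 67% | about 5% |

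Only about 2–3% of trials show a significant interaction in the direction that would suggest under-replacement.

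**The same signal from opposite truths (16%/25%).** With no prognostic effect in the placebo arm and a true interaction odds ratio of 0.8, the NRT slope is significantly negative in 59% of trials. With a common odds ratio of 0.8 and no interaction, it is also 59%. At 0.7 both figures are 93%. The one-arm slope cannot tell these situations apart.

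**Power of the interaction.** By the approximation: odds ratio 0.8, 0.223/0.156 = 1.43, Φ(1.43 − 1.96) ≈ 30%; odds ratio 0.7, 0.357/0.156 = 2.29, Φ(2.29 − 1.96) ≈ 63%. The simulation gives about 30%, and 56–61% depending on the placebo slope.

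**The case against.** The case for leaving the text alone has four parts.

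- **The wording is hedged.** The protocol says only that a decline could point to inadequate replacement. It sets no test, threshold or conclusion for the slope. This stands, and the text should not be described as a decision rule. But the hedge does not name the comparison that would make the reading safe.
- **The right analysis is already planned.** The same model contains treatment group and is meant to examine effect modification and efficacy at given cotinine levels. This stands too. It makes the fix small, but the inference about replacement is still attached to the other contrast.
- **The premise is outside the documents.** They do not say that women with higher cotinine quit less in both arms. Correct: the size of the problem is conditional, and with no prognostic effect the false-signal rate is about 2%. The logical point does not need the premise, because the one-arm slope cannot establish whether it is true, whereas the placebo arm can.
- **The simulated rates may be high.** They assume a cotinine value for all 525 women per arm, while the enrolment data record only that a blood sample was requested. Fewer values would give fewer significant slopes, and also less power for the interaction.

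A reader might go further and infer that a conclusion of under-replacement drawn from this slope would usually be false, or would appear almost whatever the truth. The figures do not support that. They give the chance of a signal when there is no under-replacement. The share of signals that are false also depends on how likely under-replacement is, and no section gives that.

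**Conclusion.** The point holds as a fault in one stated interpretation within a secondary analysis. A decline in the NRT group alone is not specific to inadequate replacement. If cotinine is equally prognostic in both arms, at an assumed odds ratio of 0.9 to 0.7 per SD, and the patch effect is constant, the slope misleads in about 17% to 93% of trials at the planned quit rates and about 11% to 67% at 8%/10%. The interaction keeps its nominal 5%. The range is wide because the prognostic strength is assumed.

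The effect-modification part of the plan is sound. The primary comparison is untouched. Even a significant interaction would be suggestive of under-replacement, not proof of it.

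**What to change.** Reword the last part of the cotinine paragraph in d) Sub group analyses so that:

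- any statement about inadequate replacement rests on the treatment-by-cotinine interaction, that is, on an NRT slope steeper than the placebo slope;
- the NRT versus placebo effect is reported with confidence intervals at stated cotinine levels;
- the NRT-arm slope is presented beside the placebo slope and labelled descriptive.

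This needs no new data and no change to the model. The cost is caution: given the modest power shown above, a non-significant interaction should not be read as evidence that replacement was adequate, and the confidence intervals should carry the message.

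The one-month visit offers a tempting shortcut: "A saliva sample to measure cotinine levels on treatment will be taken". Comparing that value with baseline saliva only in validated abstainers on NRT should not be put forward as direct evidence on replacement. It selects on a post-randomisation success and so leaves out women who relapsed for want of nicotine. Cotinine levels are also affected by the faster clearance in pregnancy (140% higher for cotinine, according to the Background).
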